**Exploratory and Clinical Analyses:**
**Risk Factors for Clinical Hyperkalemia:** As an exploratory analysis, a multivariable logistic regression will be performed to identify risk factors for the development of clinically significant hyperkalemia (defined as serum potassium > 5.0 mmol/L).**Subgroup Analysis:** Subgroup analyses will be conducted based on key clinical factors, including **preoperative renal function (e.g., stratified by eGFR categories)** and bronchial blocker usage.**Assessment of Acid-Base Components:** Changes in other acid-base parameters (e.g., HCO₃ ⁻ , BE, anion gap) will be descriptively analyzed.

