**Analyses of Factors Associated with Potassium Increase:**
**Correlation Analysis:** To explore potential physiological drivers, correlations between the change in serum potassium (ΔK⁺) and changes in other variables will be assessed. These variables will include the change in PaCO₂ (ΔPaCO₂) and markers of metabolic stress, such as the change in lactate (ΔLac).**Multivariable Analysis of** Δ**K** ⁺ **:** A multivariable linear regression analysis will be performed to identify factors independently associated with the magnitude of the serum potassium increase (ΔK⁺). Candidate covariates for the multivariable model include the change in PaCO₂ (ΔPaCO₂), change in lactate (ΔLactate), baseline eGFR, fluid balance, norepinephrine dose, and the duration of the prone position. The final selection of independent variables will be determined based on clinical relevance, assessment of multicollinearity (e.g., variance inflation factor), and the sufficiency of outcome events to avoid overfitting.

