### Sample size estimation

The sample size calculation is based on the study’s primary outcome: the mean difference in serum potassium levels within the prone-position cohort. Our preliminary data from 50 cases indicate that serum potassium concentration increases by a mean of 0.73 mmol/L (standard deviation [SD] 0.53) during the prone phase. While this large effect size would allow for statistical significance with a very small sample, we aimed to power the study to detect a more conservative, yet still clinically significant, difference of 0.5 mmol/L. Although the precise threshold for adverse cardiovascular effects associated with an acute potassium increase remains undefined, the relationship between serum potassium and cardiovascular events typically follows a U-shaped curve [5]. Recent evidence further suggests that the magnitude of potassium increase is a significant predictor of arrhythmias [6]. Therefore, in the clinical setting of esophagectomy, we considered a 0.5 mmol/L increase to be a clinically relevant safety margin. Assuming a paired t-test with a two-sided alpha of 0.05 and a power of 80%, a minimum of 34 patients in the prone-position cohort is required.

We plan to include all eligible patients from both institutions within the study period (January 2022 - December 2024), targeting a total sample size of approximately 150 cases. While the primary power calculation is met with 34 patients, this larger sample size will provide robust data for the secondary outcomes, including the multivariable regression analyses, ensuring greater precision and the ability to explore multiple predictor variables.

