#### Analyses for secondary outcomes.

**Analyses of Factors Associated with Potassium Increase:** For correlation analysis, Pearson or Spearman correlation will be used. For multivariable analysis of ΔK ⁺ , a linear regression model will be developed.**Sensitivity Analysis:** The primary outcome will be re-analyzed using a paired t-test on the subset of patients excluding those with severe metabolic acidosis.**Exploratory and Clinical Analyses:** For identifying risk factors for clinical hyperkalemia, a multivariable logistic regression model will be used. For subgroup analyses, the primary outcome will be compared between strata (e.g., using an independent t-test or ANOVA). Other exploratory analyses will be descriptive or use appropriate statistical tests as needed.

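### Risk factors for potassium above 5.0 mmol/L are sought only through an exploratory logistic model on the cut value, and the planned full-scale model does not list baseline potassium

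*Protocol article*

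**What the plan says.** In the protocol article, the section Exploratory and Clinical Analyses plans, as an exploratory analysis, that "a multivariable logistic regression will be performed to identify risk factors for the development of clinically significant hyperkalemia (defined as serum potassium > 5.0 mmol/L"). No timepoint is named, and Timepoint 2 (the prone phase) is the natural inference. The section Analyses for secondary outcomes repeats the method: "For identifying risk factors for clinical hyperkalemia, a multivariable logistic regression model will be used".

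A full-scale factor analysis is planned separately, under Analyses of Factors Associated with Potassium Increase: "A multivariable linear regression analysis will be performed to identify factors independently associated with the magnitude of the serum potassium increase (ΔK"⁺). Its six candidates are the changes in PaCO₂ and lactate, plus "baseline eGFR, fluid balance, norepinephrine dose, and the duration of the prone position". Baseline potassium is not among them. The list is of candidates, and final selection is left open.

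On numbers, Sample size estimation describes "targeting a total sample size of approximately 150 cases" and adds that "this larger sample size will provide robust data for the secondary outcomes, including the multivariable regression analyses, ensuring greater precision".

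**The concern.** Potassium is read as a continuous value on every blood gas. Cutting it at 5.0 mmol/L treats 4.1 and 4.9 as the same and 4.9 and 5.1 as different. The information in a logistic model is then governed by how many patients fall above the cut, not by 150.

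Two consequences follow. First, a factor that truly raises potassium may be significant in the linear model and not in the logistic one because of the cut alone, and readers could take that disagreement for physiology. Second, a non-significant term for PaCO₂, eGFR or norepinephrine in a model of clinically significant hyperkalemia could be read as reassurance.

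The linear model would be the natural place to recover the lost information. Without baseline potassium, however, it answers a question about the change only and cannot be turned into a statement about reaching 5.0 mmol/L for a patient with a given starting value.

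**Working it through.** **The plan's own figure.** The article gives no power, event rate or effect size for the logistic model, so there is nothing to reproduce. Its only required sample size, 34, belongs to the primary paired t-test and does not enter here.

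**Inputs from Sample size estimation:** mean rise 0.73 mmol/L, SD 0.53, about 150 patients, two-sided alpha 0.05. **From the linear-model section:** six candidate covariates. **Assumed, because the article does not give them:** baseline mean 3.6 to 4.2 mmol/L, baseline SD 0.35, baseline independent of the rise, independent covariates, and a factor correlated r = 0.20, 0.25 or 0.30 with the rise.

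**Step 1: expected events.** Timepoint 2 potassium has mean (baseline + 0.73) and SD √(0.35² + 0.53²) = √0.4034 = 0.635. For baseline 3.6, P(K > 5.0) = 1 − Φ((5.0 − 4.33)/0.635) = 1 − Φ(1.055) = 14.6%. For 3.8, 4.0 and 4.2 it is 23.0%, 33.5% and 45.6%. In 150 patients that is about 22, 34, 50 and 68 events. With seven terms (six covariates plus baseline potassium) there are about 3, 5, 7 and 10 events per term.

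**Step 2: power by simulation** (500 replicates per cell). Both models contain the six covariates and baseline potassium; one takes Timepoint 2 potassium as it is, the other takes K > 5.0. Entries are linear / logistic (loss in points).

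| Baseline mean | r = 0.20 | r = 0.25 | r = 0.30 |
|---|---|---|---|
| 3.6 | 67.8 / 28.0 (39.8) | 85.6 / 40.2 (45.4) | 96.8 / 58.6 (38.2) |
| 3.8 | 63.0 / 34.6 (28.4) | 85.8 / 53.8 (32.0) | 94.8 / 69.2 (25.6) |
| 4.0 | 69.4 / 43.2 (26.2) | 87.6 / 56.4 (31.2) | 96.2 / 77.2 (19.0) |
| 4.2 | 66.6 / 41.2 (25.4) | 85.4 / 60.4 (25.0) | 94.6 / 77.4 (17.2) |

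The losses run from 17.2 to 45.4 points. The Monte Carlo standard error of one power is at most √(0.25/500) = 2.2 points, so roughly 15 to 45 is a fair statement. When cells with a baseline-to-rise correlation of −0.3 were included, the range was 11 to 46. Likelihood-ratio tests in place of Wald tests recovered only 1 to 4 points.

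**Step 3: check by formula.** For a normal outcome cut so that a share p lies above c = z(1−p), the relative efficiency is φ(c)²/[p(1−p)], and power after the cut is Φ((1.960 + z of full-scale power)·√efficiency − 1.960). At 80% full-scale power and p = 15%, the efficiency is 0.426 and Φ(2.802 × 0.653 − 1.960) = Φ(−0.13) = 45%, a loss of 35 points. At p = 35% the efficiency is 0.603 and power is 59%, a loss of 21. At p = 10% the loss is 43, and at 50% it is 19. Formula and simulation agree.

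**Step 4: what the linear model already covers.** Since K₂ = K₁ + ΔK, fitting ΔK = a + bK₁ + cX + e is the same as fitting K₂ = a + (b + 1)K₁ + cX + e. The coefficient c, its standard error and its p-value are identical. Adding K₁ to the planned ΔK⁺ model therefore is the full-scale model of the level reached.

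**Step 5: what leaving out baseline can cost.** If baseline is unrelated to the rise or to the factor, little. If it relates to both, the factor's coefficient absorbs part of the baseline effect. Illustration in standardised units: factor effect 0.25, baseline effect on the rise −0.3, factor-to-baseline correlation 0.3. The unadjusted coefficient is 0.25 − 0.3 × 0.3 = 0.16, and power is about Φ(0.16 × √150/√(1 − 0.16²) − 1.960) = Φ(0.03) = 51%. Adjusted, the residual variance is 1 − (0.0625 + 0.09 − 0.045) = 0.8925, and power is about Φ(0.25 × √0.91 × √150/√0.8925 − 1.960) = Φ(1.13) = 87%. This ignores the other five covariates. Simulations with relations of this kind gave about 37 to 56% unadjusted and 86 to 93% adjusted.

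**The case against.** The strongest reply is that the full-scale factor analysis is already in the plan and ranks above the cut one. The article calls the logistic model exploratory, and by the identity in Step 4 the replacement is just the planned ΔK⁺ model with one more covariate. When baseline is unrelated to the rise, as in the Step 2 table, the planned model has nearly the same power without that covariate. All of this stands, and it is why the point is minor.

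It is also fair that crossing a threshold is a legitimate clinical question, that pairing a continuous with a threshold model is ordinary reporting, and that a condensed article need not cite a source for the cut. The recommendation therefore keeps both the threshold and the logistic model. Greater precision with 150 than with 34 patients holds for any model, and the article claims no power for the logistic one. Even so, its promise of robust data covers the multivariable regressions in the plural, and 22 to 34 events over seven terms would not be robust.

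The article does make variable selection depend on sufficient outcome events. That sentence sits under the linear model, and fewer terms would not undo the information lost by the cut.

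A reader might infer that the study forgoes a full-scale search for drivers of potassium, or will treat null logistic terms as proof of safety. The article supports neither. The linear model and the correlations are planned, and the Discussion rests its monitoring advice on the primary comparison and its inference about predictors on the magnitude of the increase.

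**Conclusion.** The point holds as a minor one. Factors for exceeding 5.0 mmol/L are sought only on the cut value, and baseline potassium is missing from the listed candidates of the model that could answer the question on the full scale. The cost is roughly 15 to 45 points of power for the exploratory logistic analysis, larger when events are few. That range is conditional on the assumed baseline mean and SD, the assumed factor correlations and roughly normal values. No single figure can be attributed to the article, because it gives neither an event rate nor a baseline potassium; an event share of 5%, for example, would give a loss of about 54 points at 80% full-scale power. The primary outcome is unaffected.

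**What to change.** 1. Under Analyses of Factors Associated with Potassium Increase, add Timepoint 1 potassium as a covariate in the linear model of ΔK⁺, and state that this is equivalent to modelling Timepoint 2 potassium adjusted for baseline.
2. Under Exploratory and Clinical Analyses and Analyses for secondary outcomes, take from that model the predicted probability of exceeding 5.0 mmol/L at chosen values of each factor: 1 − Φ((5.0 − fitted Timepoint 2 mean)/residual SD). Report the observed number and percentage above 5.0 mmol/L beside it.
3. Keep the logistic model as supportive, name its timepoint, and state that non-significant terms will not be read as absence of risk.
4. In Sample size estimation, limit the claim of robust data to the continuous-outcome models.

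The cost is wording: Timepoint 1 potassium is already to be collected, no patients are added, and the article states that extraction and analysis have not begun. The downside is that the predicted probabilities depend on the residual distribution. This can be checked, or the empirical residuals can be used in place of the normal curve.

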### Exclusion criteria

● Patients undergoing chronic dialysis ● Patients with severe electrolyte abnormalities (defined as a preoperative serum potassium level of 5.0 mmol/L or higher) ● Patients who received intraoperative massive transfusion (defined as having received a transfusion for a blood loss of 2000 mL or more).

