### Data collection

The following data will be collected from medical records: ● **Patient demographics:** Age, sex, BMI, ASA PS ● **Preoperative status:** eGFR, history of diabetes, hypertension, respiratory dysfunction or heart disease, perioperative use of diuretics, insulin, or β2-agonists. ● **Procedural details:** ○ Surgical approach (e.g., thoracoscopic, robot-assisted, or open thoracotomy) ○ Anesthesia method ○ Surgical time, Anesthesia time ○ Duration in the prone position ○ CO₂ insufflation (presence, duration, and pressure) ○ Bronchial blocker usage ● **Hemodynamics and fluid balance:** ○ The minimum mean arterial pressure (MAP) during the main surgical phase (prone phase) ○ Intraoperative urine output, Fluid volume, Blood transfusion status ○ Norepinephrine use and total dose ● **Arterial blood gas data:** ○ Serum potassium, pH, PaCO₂, HCO₃ ⁻ , BE, AG, and lactate will be collected at the following three timepoints: ■ **Timepoint 1 (Baseline):** After induction of anesthesia, before surgical positioning or incision. ■ **Timepoint 2 (Intervention):** During the phase of maximal respiratory challenge (e.g., the point of highest PaCO₂ during prone positioning with capnothorax). In cases where arterial blood gas was measured multiple times during the prone phase, the data from the timepoint with the lowest arterial pH will be used for the primary analysis. ■ **Timepoint 3 (Post-procedure):** Immediately upon arrival in the ICU or at the end of surgery.

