### Statistical analysis

The selection of the blood gas sample with the lowest pH during the intervention phase is a pre-specified criterion. This approach is not considered a selection bias but is rather a deliberate strategy to focus the analysis on the study’s primary research question: the physiological response, particularly in potassium homeostasis, to the most severe degree of acute acidosis encountered during the procedure.

All statistical analyses will be performed using R version 4.3.2 (R Foundation for Statistical Computing, Vienna, Austria). A p-value of less than 0.05 will be considered statistically significant.

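### The exploratory hyperkalemia outcome names no timepoint, and the only prone potassium listed for collection is chosen by lowest pH, so some potassium peaks above 5.0 mmol/L may go uncounted

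*Protocol article*

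**What the plan says.** All of this is in the Protocol article.

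- **Outcome** (Exploratory and Clinical Analyses): a multivariable logistic regression for risk factors for "development of clinically significant hyperkalemia (defined as serum potassium > 5.0 mmol/L"). No timepoint, window or baseline condition is given. The statistical section on secondary outcomes adds only the type of model.
- **Values collected** (Data collection): potassium and the other blood gas values "will be collected at the following three timepoints". Timepoint 1 is "After induction of anesthesia, before surgical positioning or incision". Timepoint 2 is the prone phase, with "the point of highest PaCO₂ during prone positioning with capnothorax" given as an example. Timepoint 3 is "Immediately upon arrival in the ICU or at the end of surgery".
- **Choice among several prone gases** (Data collection): "the data from the timepoint with the lowest arterial pH will be used for the primary analysis".
- **Reason for that choice** (Statistical analysis): "The selection of the blood gas sample with the lowest pH during the intervention phase is a pre-specified criterion". The justification offered is the response of potassium to the most severe acidosis, which is the primary research question.
- **Eligibility** (Exclusion criteria): severe electrolyte abnormality is excluded, "defined as a preoperative serum potassium level of 5.0 mmol/L or higher".

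**The concern.** The event is defined on potassium, while the prone sample is chosen on pH. The two need not coincide. Take an invented patient with potassium 4.8 at pH 7.18 and 5.4 in a later prone gas at pH 7.22. The kept prone value is 4.8. Unless Timepoint 1 or Timepoint 3 also exceeds 5.0, this patient enters the model as a non-case.

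There is a smaller problem in the other direction. The exclusion uses the preoperative potassium, whereas Timepoint 1 is a later sample, after induction. A patient below 5.0 before surgery, at 5.1 at Timepoint 1 and unchanged in the prone phase meets the numerical definition without having crossed the threshold during the exposure.

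This is the only listed outcome framed as a clinical event. It also matters when the gap is closed. A later analysis plan can choose among values that were extracted, but it cannot restore values that were not. The Study status section says the data will be fully anonymized before analysis, so going back to the records may be difficult.

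**Working it through.** The plan gives no figure for this outcome, so there is nothing to reproduce. The size has to be simulated, mostly from assumed inputs.

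**Inputs from the Protocol article (Sample size estimation):** mean prone rise 0.73 mmol/L, SD 0.53, from 50 preliminary cases; target of about 150 patients.

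**Inputs assumed:** Timepoint 1 potassium 4.0 (SD 0.35); mean rise per prone gas 0.65 with total SD 0.53; 1 to 4 prone gases per patient; within-patient SD of potassium between prone gases, s, of 0.15 or 0.25; within-patient correlation between acidity and potassium, r, of 0 or 0.5.

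**Model.** Potassium in gas j = Timepoint 1 value + patient's mean rise + s × (r × acidity_j + √(1 − r²) × noise_j). The kept gas is the most acid one. Missed share = 1 − P(kept K > 5.0) / P(highest prone K > 5.0). There were 400,000 simulated patients per setting.

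**Check by hand, one gas.** Potassium has mean 4.0 + 0.65 = 4.65 and SD √(0.35² + 0.53²) = 0.635. P(K > 5.0) = 1 − Φ(0.35 / 0.635) = 1 − Φ(0.551) = 0.29, which matches the simulation.

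| Prone gases | s | Missed, r = 0.5 | Missed, r = 0 |
|---|---|---|---|
| 1 | either | 0% | 0% |
| 2 | 0.15 | 7% | 14% |
| 2 | 0.25 | 11% | 21% |
| 3 | 0.15 | 10% | 19% |
| 3 | 0.25 | 15% | 29% |
| 4 | 0.15 | 12% | 23% |
| 4 | 0.25 | 17–18% | 34% |

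With three gases, s = 0.25 and r = 0.5, the kept gas records 34.9% of patients as hyperkalemic, against 41.0% with any prone gas above 5.0. If all 150 patients had three gases, the difference would be 150 × 0.061, about 9 patients.

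**Calibration.** At r = 0.5 with two to four gases, the mean rise in the kept gas is 0.69 to 0.78, which brackets the protocol's 0.73. At r = 0 it stays at 0.65. The r = 0.5 column therefore fits the preliminary data better, and the r = 0 column is an outer bound.

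**A second construction.** Here the kept gas rises by 0.73 (SD 0.53), and one to three other prone gases differ from it by a mean of −0.1 (SD 0.15 to 0.3). Preoperative potassium has mean 3.8 to 4.2 and SD 0.3 to 0.4, cut off below 5.0, and the post-induction value differs from it with SD 0.2 to 0.3. The missed share is then about 3% to 31%.

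**Patients already above 5.0 at Timepoint 1.** In the first model, 1 − Φ(1.0 / 0.35) = 1 − Φ(2.86) = 0.2% of patients. In the second, which applies the preoperative exclusion, 0.05% to 4%: 150 × 0.0005 = 0.1 to 150 × 0.041 = 6, so 0 to 6 of 150.

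**Dependence of the peak on sampling.** With s = 0.25, P(highest prone K > 5.0) is 29% with one gas and 44% with four, in otherwise identical patients.

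**The case against.** **The lowest-pH rule is worded for the primary analysis.** The logistic outcome is not tied to that gas, and the Discussion speaks of serial blood gas data. A reader might infer that the plan restricts hyperkalemia to the lowest-pH gas. It does not say so. What stands is that no other prone potassium is listed for collection, so as written the model has no other prone value to use.

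**A condensed article may leave the window of an exploratory outcome to the analysis plan.** That is fair for the choice of timepoint. It does not cover the list of values to be extracted, which this article does fix.

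**The preoperative exclusion removes known hyperkalemia, and the word development may already imply a new event.** Both are fair. A reader might infer that prevalent cases in general are counted as developed. The text supports only a residual group, below 5.0 before surgery and above it after induction, whose handling is not stated.

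**Peak potassium has its own bias.** It depends on how often gases were drawn, and the Discussion acknowledges that timing was variable. At zero correlation the whole missed share is this sampling effect, because the kept-gas rate stays at 29% whatever the number of gases. The objection stands, and it shapes the fix.

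**The missed share compares prone gases only.** If a Timepoint 3 value above 5.0 also makes a patient a case, some are recovered and the share is lower.

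Two further inferences are not supported. That the odds ratios are biased towards factors driving pH is plausible, but it was not examined here. That the Discussion's argument for monitoring rests on this endpoint is also too strong: it is conditioned chiefly on confirming a potassium increase, which is the primary outcome.

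**Conclusion.** The point holds in a limited form. The hyperkalemia outcome has no stated timepoint or baseline condition, and the one prone potassium listed for collection is selected on pH, so it is not built to capture peak potassium.

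For patients with two to four prone gases, about 7% to 18% of those exceeding 5.0 in some prone gas would be missed at a correlation of 0.5, and up to about a third at zero correlation. Nothing is missed with a single prone gas. Everything except the rise of 0.73 and SD of 0.53 is assumed, and the documents do not give the number of prone gases per patient. The Timepoint 1 problem is small, at most a handful of patients.

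The analysis is labelled exploratory, and the paired primary analysis and the other analyses of the change in potassium are untouched. Severity is minor to moderate. The reason to act is timing: the remedy is cheap before extraction and hard to apply afterwards.

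**What to change.** Before extraction begins:

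1. In Data collection, add the highest potassium among all prone-phase gases and the number of prone gases per patient.
2. In Exploratory and Clinical Analyses, define a case as peak prone potassium above 5.0 mmol/L among patients whose Timepoint 1 potassium is 5.0 or lower. Report patients above 5.0 at Timepoint 1 separately.
3. Include the number of prone gases in the logistic model, or show results by that number.
4. Report the lowest-pH-gas definition as a sensitivity analysis.
5. Leave Timepoint 2 as it is for the analyses of the change in potassium.

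The cost is one extra potassium value and one count per patient, from gases that already have to be read to find the lowest pH. The downside is that peak potassium rises clearly with the number of gases taken (29% with one against 44% with four in the illustration above). The count must therefore be accounted for in the analysis and not merely reported, and it uses one more term in an exploratory model.

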### Participants

All adult patients who underwent esophageal cancer surgery, including robot-assisted procedures, in the prone position between January 2022 and December 2024 at Aichi Medical University Hospital and Aichi Cancer Center will be included. Patients with pre-existing chronic kidney disease (not requiring dialysis) are eligible for inclusion, and the influence of baseline renal function will be evaluated as a pre-planned subgroup analysis.

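### The dedicated renal-function analysis compares the potassium rise across eGFR categories; if the relation is roughly linear, a slope on the recorded eGFR values would be clearly more powerful, at one sentence of cost

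*Protocol article*

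**What the plan says.** Four places in the protocol article bear on this.

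- **Participants.** Non-dialysis chronic kidney disease is allowed, and "the influence of baseline renal function will be evaluated as a pre-planned subgroup analysis".
- **Outcomes, Exploratory and Clinical Analyses.** The subgroups include "preoperative renal function (e.g., stratified by eGFR categories"), together with bronchial blocker use. No number of categories and no cut points are given.
- **Analyses for secondary outcomes.** "For subgroup analyses, the primary outcome will be compared between strata (e.g., using an independent t-test or ANOVA").
- **Analyses of Factors Associated with Potassium Increase.** The linear regression of the potassium change has six candidates: change in PaCO₂, then "change in lactate (ΔLactate), baseline eGFR, fluid balance, norepinephrine dose, and the duration of the prone position". The final set is open: "The final selection of independent variables will be determined based on clinical relevance, assessment of multicollinearity", with avoidance of overfitting as a further criterion.

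Under Data collection, eGFR is listed among the preoperative items ("eGFR, history of diabetes, hypertension, respiratory dysfunction or heart disease"), so a value for each patient will be available. No power, effect size or eGFR distribution is given for the renal analysis.

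**The concern.** There is no comparator arm. A comparison of the potassium change between eGFR strata is therefore simply a test of whether the change depends on eGFR. Cutting a measured value into groups ignores differences within each group, and ANOVA on three or more groups also ignores their order and spends extra degrees of freedom.

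The regression section does not supply the same answer. eGFR may or may not be retained there. If it is retained, its coefficient is conditional on PaCO₂ change, lactate change, fluid balance, norepinephrine dose and prone duration. All of these arise after baseline, and some may lie on the path from renal function to potassium. That coefficient is not the overall influence of baseline renal function that the Participants section promises. The correlation analysis concerns changes in variables and does not name baseline eGFR.

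At stake is a secondary message. A non-significant category test at 50 to 60% power could be read as showing that renal function does not matter, although patients with kidney disease are included and the Discussion treats renal dysfunction as a source of vulnerability to hyperkalemia.

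**Working it through.** The plan gives no figure for this analysis to reproduce. Its stated minimum of 34 patients belongs to the primary paired test and is not used here.

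**Inputs from the protocol article:** n = 150 (Sample size estimation, approximate target); SD of the potassium change 0.53 mmol/L (same section); significance at p < 0.05 (Statistical analysis).

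**Assumptions:** eGFR normal with mean 70 to 75 and SD 15 to 18; a linear relation; complete data; a correlation that puts the slope test near 80% power.

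**1. Correlation.** For 80% power, r = tanh[(1.96 + 0.84)/√(150 − 3)] = tanh(2.80/12.12) = 0.227, rounded to 0.23. In units this is 0.23 × 0.53 = 0.12 mmol/L per SD of eGFR. With an SD of 18 or 15 that is 0.12/1.8 = 0.07 or 0.12/1.5 = 0.08 mmol/L per 10 mL/min/1.73 m².

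**2. Information kept by one cut.** If a fraction q lies below the cut c (in SD units), efficiency relative to the continuous scale is φ(c)²/[q(1 − q)].

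- Median split: 0.399²/0.25 = 0.64
- Cut at 60, mean 75, SD 15 (c = −1, q = 0.16): 0.242²/(0.159 × 0.841) = 0.44
- Cut at 60, mean 70, SD 15 (q = 0.25): 0.54

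Approximate power is Φ(√efficiency × 2.80 − 1.96) when the slope test has 80%. A median split gives Φ(0.80 × 2.80 − 1.96) = 61%. A 15/85 split (efficiency 0.43) gives 45%.

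**3. Simulated power under a linear relation** (n = 150, r = 0.23, 4000 studies per setting; Monte Carlo standard error at most √(0.25/4000) = 0.8 points):

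| Test of renal influence | df | Power |
|---|---|---|
| Slope on continuous eGFR | 1 | 81–83% |
| 3-knot spline, joint test | 2 | 72–74% |
| Cut at 60, t-test | 1 | 47–57% |
| Cuts at 60 and 90, ANOVA | 2 | 57–61% |
| Cuts at 45, 60 and 90, ANOVA | 3 | 52–57% |

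With category power taken as about 47 to 60%, the loss against the slope is about 82 − 60 = 22 to 82 − 47 = 35 points. Against the joint spline test it is about 72 − 60 = 12 to 73 − 47 = 26 points.

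**4. Other linear settings.** With the slope test's power set anywhere from 50% to 95%, and two to five categories, the loss against the slope runs from about 12 points (tertiles, at 95%) to about 44 points (a 10/90 split, at 80%).

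**5. Non-linear truth.**

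- *Abrupt step of 0.3 mmol/L below 60, eGFR mean 70, SD 18:* slope 63–64%, spline 62–63%, cut at 60 86%, cuts at 60/90 80%, cuts at 45/60/90 73%.
- *Same step, mean 75, SD 15:* slope 36–38%, cut at 60 69%.
- *Gradient only below 60 (0.03 mmol/L per unit):* categories range from about 6 points worse to 12 points better than the slope; the spline does best.

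**The case against.** **A reader might infer an unconditional loss of 20 points or more.** The documents do not support that. They give no eGFR distribution, no correlation and no shape for the relation. The size depends on a linear truth and on the 1-df slope as comparator. With a step at the cut, the category test wins by 10 (73 against 63%) to 33 points (69 against 36%). Because the Participants section frames the question around existing kidney disease, a threshold is not far-fetched. This objection stands, and every figure here is conditional. The advantage of categories does, however, need the cut to sit on the true step, and the article names no cut.

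**A reader might infer that a renal gradient would go unseen.** That is too strong. The candidates "baseline eGFR, fluid balance, norepinephrine dose, and the duration of the prone position" put eGFR, with no mention of categories, into a planned regression of the same outcome. Nothing in the selection criteria points to dropping it, and six covariates in 150 patients is not excessive. So a second look is likely. It remains a look at a different quantity, for the reason given under the concern.

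**A reader might object to the open cut points in themselves.** A condensed article may leave these to the full protocol or analysis plan, so their absence is not the point.

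**The analysis is exploratory and worded by example.** Both the categories and the tests are introduced with e.g., and no power is claimed. That limits the severity. It also means that a continuous analysis can be adopted without contradicting the text.

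**Conclusion.** The point holds in a limited, conditional form. The dedicated evaluation of renal function is a test across eGFR categories, although eGFR is collected for each patient, and the candidate-covariate regression does not replace it. Under a roughly linear relation with r about 0.23, n = 150 and normally distributed eGFR, grouping lowers power from about 82% (1-df slope) to about 47 to 60%. Against a 2-df spline test at 72 to 74% the loss is about 12 to 26 points. An abrupt step at the chosen boundary can reverse the ranking.

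The primary outcome, its sample size and the main conclusion are not affected. Label: cheap improvement, low severity.

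**What to change.** In Participants, the Subgroup Analysis item and Analyses for secondary outcomes, state the following for renal function:

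- **Deciding test:** a linear regression of the potassium change on baseline eGFR as a continuous variable. The 1-df slope decides and is reported per 10 mL/min/1.73 m² with its 95% CI.
- **Shape:** a pre-set 3-knot spline, used only as a check of non-linearity. If the joint 2-df test decided instead, about 8 to 11 points of the power gain would be given up (82 − 74 to 83 − 72).
- **Adjustment:** baseline variables only, such as age and sex, if any.
- **Categories:** the mean potassium change by eGFR category, with boundaries fixed before data access, as a descriptive table without tests.

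The between-strata t-test can stay for bronchial blocker use.

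**Cost:** about one sentence of analysis wording, with no extra data or patients. Data extraction had not begun when the article was written, so the change can still count as pre-specified if it is made before data access. The downside is lower power if the true effect is a step at a category boundary; the spline check and the table would help to show such a pattern.
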